## **2. Online group discussions with country trainers**

### ***RE-AIM elements: Implementation, Maintenance***

Transcripts of the online group discussions with country trainers are immediately available and already in English. They will be analyzed following the principles of thematic analysis – in a theoretical/deductive ‘top down’ way, meaning that we already chose to pre-structure the themes to some extent. As a first step of analysis transcripts will be read and reread to allow the researchers to become thoroughly familiar with the data. Codes will then be ascribed to meaningful text units and grouped together. The findings will be discussed with different members of the research team, in order to work toward a consensus about interpretation of the key findings.

## **3. Structured diaries for country trainers and PACE coordinators**

### ***RE-AIM element: Implementation***

In addition to quantitative information, the diaries for country trainers and PACE coordinators contain open-ended questions on successes and challenges that they encounter during PACE activities.

Per LTCF, successes as well as challenges will be analyzed by ascribing codes to the answers of PACE coordinators and country trainers. Then, these codes will be grouped together. The findings will be discussed with different members of the research team, in order to work toward consensus about interpretation of the key findings.

## **COMBINING RE-AIM ELEMENTS**

There is no validated strategy to combine RE-AIM elements into one overall score. One approach to combine the different RE-AIM elements is to visually display how each LTCF within each country scores on each RE-AIM

dimension. Based on the key elements of the PACE Program and each RE-AIM dimension, and based on the (range of) descriptive statistics and other outcomes that we will gather with above described measurement methods, we will define the criteria for a low, medium and high level of Reach, Adoption, Efficacy, Implementation and Maintenance. We can visually display how each LTCF within each country performed on the different dimensions. In this way, the strengths and limitations of implementing the PACE Program in different LTCFs and countries can quickly be seen (see Figure 2 for an example).

**Figure 2. Example of visually displaying RE-AIM dimensions.**

[figure not shown]

### III. Cost-effectiveness evaluation plan – prepared by Radboud UMC

Section III contains the cost-effectiveness analysis plan. This section includes the plan on how to evaluate the cost-effectiveness of the ‘PACE Steps to Success’ palliative care programme in comparison to end-of-life care provided as usual.

#### DATA COLLECTION

Data were collected within the PACE Study II project. Retrospective data collection of deceased residents took place at the start of the trial (month 1) and at month 13 and 17 of the trial.

PACE staff questionnaires regarding care services received during the *last month of life* are used to determine resource use by residents from. Direct medical resource use was collected on a per patient basis in the participating facilities, using (parts of) the resource use in dementia (RUD). Direct medical costs include care received in the last months of life, such as hospital admission, care received in an emergency room, treatments in the last month of life, adverse events in the last month of life, or opioids, antipsychotics, hypnotics or sedatives. Additionally, data on PACE-related costs are also collected.

#### Calculating costs

The cost to be calculated will include direct medical costs and the PACE-related costs. Cost calculation will be the product of volumes of resource use multiplied by prices. After resources use data were gathered, costs were estimated by multiplying quantities of resources used with standard unit cost prices in Euros, based on Dutch prices. Maximum tariffs for unit costs as set by the Dutch Health Care Authority (NZA) were used where possible. If no maximum rates are specified, ‘passers-by’ hospital tariffs were used. The price vector will be adjusted for differences in price levels across countries, using the purchasing power parity (PPP) technique.

#### DATA ANALYSIS

A resident-based economic evaluation based on the general principles of a cost-effectiveness (utility) analysis was performed to analyze the cost-effectiveness of the ‘PACE 6 Steps to Success’ palliative care programme in comparison to palliative care provided as usual.

#### Outcome measures

Primary outcome measures for the economic evaluation, considering last month before dying, are direct costs and quality-adjusted life years (QALYs), which will be based on scores on the EuroQol-5D (EQ5D-5L) as well as the Quality of Dying in Long-term Care (QOD-LTC) measure.

### **Incremental cost-effectiveness ratio**

Incremental cost-effectiveness ratios (ICERs) 'cost per quality increase based on EQ5D-5L utilities' as well as 'cost per quality increase as measured by the QOD-LTC' will be computed. Uncertainty surrounding the ICERs will be determined by using the bootstrap method or the Fieller method.

The ICER (cost per QALY gained) will be transformed in the parameter 'Net Monetary Benefit'. In a regression approach Net Monetary Benefit is the dependent variable. Independent variables are group (PACE, control), LTCF (cluster) and potential confounders. We will estimate 6 models, varying the WTP for a QALY over a range [€0-€100.000] in steps of €20.000 and present the results via a Cost-Effectiveness Acceptability Curve (CEAC). Depending on the skewness of cost (NMB with WTP=0), we will apply a generalized linear model (GLM) approach using a gamma distribution with log link function with cluster robust standard errors. For NMBs with WTP>0 we apply a GLM with log or identity link depending on skewness of the distribution, with cluster robust standard errors.

A cost-effectiveness acceptability curve will be derived that is able to evaluate efficiency by using different thresholds (willingness to pay) for a QALY. The impact of uncertainty surrounding deterministic parameters (for example prices) on the ICER will be explored using one-way sensitivity analyses on the range of extremes. Potential differences in transferability of cost and effect data between countries will be accounted for in scenario analyses.

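### Skewness decides between a log and an identity link for net monetary benefit at WTP>0, although mean NMB can be zero or negative and a log link then cannot work

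*Combined protocol and SAP*

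**What the plan says.** The point concerns Section III of the combined protocol and SAP, under Incremental cost-effectiveness ratio. The plan converts the ICER into NMB and states: "In a regression approach Net Monetary Benefit is the dependent variable". The grid is set by "We will estimate 6 models, varying the WTP for a QALY over a range [€0-€100.000] in steps of €20.000", and the results go into a cost-effectiveness acceptability curve (CEAC).

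Two sentences fix the model form. At zero willingness to pay: "Depending on the skewness of cost (NMB with WTP=0), we will apply a generalized linear model (GLM) approach using a gamma distribution with log link". Above zero: "For NMBs with WTP>0 we apply a GLM with log or identity link depending on skewness of the distribution". Both come with cluster-robust standard errors. No distribution family is named for WTP>0. Nothing is said about zero or negative values, and no conversion from the log scale to euros is described.

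The horizon is given under Outcome measures: "Primary outcome measures for the economic evaluation, considering last month before dying, are direct costs and quality-adjusted life years (QALYs". Under Calculating costs, "The cost to be calculated will include direct medical costs and the PACE-related costs", and "Cost calculation will be the product of volumes of resource use multiplied by prices", so cost cannot be negative. The plan does not write out a formula for NMB.

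**The concern.** A log link models the logarithm of the mean, so it needs a positive fitted mean. NMB is a difference between two non-trivial quantities and carries no such constraint. The one-month horizon makes the problem more likely, because it keeps the QALY term small while hospital and emergency care in that month, plus programme costs, are charged against it.

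Skewness does not tell the analyst whether mean NMB is positive. Right-skewed costs enter NMB with a minus sign and give it a long negative tail. A rule that answers skewness with a log link can therefore select that link where it is least suitable.

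The CEAC and the incremental net benefit carry the economic conclusion. A wrong link could leave points on the curve missing or meaningless, or put the estimates on a ratio scale when a euro difference is wanted.

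**Working it through.** **The plan's own figure.** The number of grid points is 100,000/20,000 + 1 = 6, which agrees with the six models stated.

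**Inputs.** WTP grid and last-month horizon: from Section III. Formula NMB = WTP x (utility x 1/12) - cost: assumed, as the standard resident-level form. Costs and utilities: assumed throughout, because the documents give neither.

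**Step 1: ceiling and break-even.** With utility no higher than 1, a resident contributes at most 1/12 = 0.083 QALY. Mean NMB is positive only if mean cost is below WTP x mean utility / 12.

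| WTP (EUR) | Ceiling, utility 1 | Break-even mean cost, utility 0.5 | Break-even mean cost, utility 0.2 |
|---|---|---|---|
| 20,000 | 1,667 | 833 | 333 |
| 40,000 | 3,333 | 1,667 | 667 |
| 60,000 | 5,000 | 2,500 | 1,000 |
| 80,000 | 6,667 | 3,333 | 1,333 |
| 100,000 | 8,333 | 4,167 | 1,667 |

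**Step 2: range over assumptions.** Twelve settings were simulated with 2,000 residents each: mean cost EUR 500, 1,500, 3,000 or 6,000 (gamma-distributed) and mean utility 0.1, 0.2 or 0.4 (SD 0.25). Overall mean NMB was negative in 11 of 12 settings at WTP 20,000 and in 6 of 12 at 100,000.

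**Step 3: fitting the permitted links.** One further simulated data set was used (2,000 residents, no clustering; control mean cost EUR 1,500, 10% lower with the programme; mean utility 0.25 and 0.28). The family was Gaussian, since the plan names none for WTP>0.

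| WTP | Mean NMB, control / programme | Difference | Log link | Identity link coefficient |
|---|---|---|---|---|
| 20,000 | -1,069 / -854 | 215 | coefficients of order 10^18 to 10^19, flagged as converged | 215 |
| 60,000 | -251 / 88 | 339 | estimation error | 339 |
| 100,000 | 567 / 1,029 | 462 | 0.596 | 462 |

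At 100,000 the log coefficient is log(1,029/567) = 0.596, a ratio of means. Only after back-transformation does it give 1,029 - 567 = EUR 462.

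The identity-link estimates lie on one line in WTP, as they should. The slope is (215.34 - 153.64)/20,000 = 0.003085 QALY, and 153.64 + 100,000 x 0.003085 = 462.

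**Step 4: WTP=0.** In the same data, gamma/log on positive cost fits, with coefficient -0.110 = log(0.896). The back-transformed cost difference is EUR -154. With the sign reversed, incremental NMB is EUR +154, equal to the identity-link result. The same model on NMB = -cost cannot be estimated.

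**The case against.** The plan can be defended on several grounds, and most of them stand.

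- A reader might infer that the WTP=0 model is impossible because every NMB value there is zero or negative. The sentence names cost, with NMB only in brackets, and gamma/log on cost is a standard model that fits. What remains is loose labelling, with no stated sign change or conversion to euros.
- A reader might infer that gamma is planned at WTP>0. It is named only in the cost sentence.
- A reader might infer that none of the WTP>0 models estimates incremental net benefit. Identity is one of the two permitted links, and it does.
- A high share of residents with negative NMB (35% to 95% at WTP 20,000 and 10% to 83% at 100,000 in the twelve settings) might be read as the failure rate. Outside the gamma family a log link needs positive means, not positive observations, so this share is not the criterion.
- A reader might infer that a log model cannot supply a CEAC point. When both arm means are positive, the log ratio is above zero exactly when the difference is. The direction is therefore preserved, and back-transformation recovers the euro amount.
- The text does not say whether the link is chosen once or at each WTP, so a curve mixing links is possible but not stated.

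The last two points have limits. The standard error of a log mean is roughly the standard error divided by the mean, and it grows without bound as an arm mean approaches zero. In one simulated trial of 1,000 residents (mean cost about EUR 1,500, no clustering, model-based standard errors), the log link at WTP 60,000 gave z = 0.5 and identity gave z = 2.75: CEAC points of about 0.70 and 0.997 from the same data. Failure is also not always visible, as the run flagged as converged shows.

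**Conclusion.** Wrong as written, of moderate severity. For the five models at WTP>0, the stated rule can select a link that the data cannot support, on a criterion that does not bear on whether it can. If log is selected and an arm's mean NMB is not positive, the model fails or gives meaningless output. If both means are positive, the coefficient is a log ratio for which no conversion is planned.

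The ceiling of WTP/12 follows from the plan's horizon and a maximum utility of 1. How often mean NMB is negative rests on assumed costs and utilities: at EUR 500 and utility 0.4 it was positive at every WTP above zero, while at EUR 6,000 it was negative throughout. At WTP=0 the fault is one of wording.

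The consequence is confined to the NMB regressions and the CEAC. Hypotheses 1 to 3 and the bootstrap or Fieller intervals for the ICERs do not depend on these models.

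**What to change.** 1. Write the definition into Section III: NMB = WTP x (utility x 1/12) - cost.
2. Use the identity link for NMB at every WTP above zero. Deal with skewness through the cluster-robust standard errors already planned, or a bootstrap that resamples LTCFs. Remove skewness as the criterion for the link.
3. At WTP=0, state that the gamma/log model is fitted to positive cost, not to NMB, and that its result is converted to a marginal euro difference with the sign reversed. Say how zero costs are handled. Alternatively, use the identity link there too, so that all six CEAC points come from one model and incremental NMB is linear in WTP.

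This is a change of wording. It needs no new data and simplifies the analysis. The price is a possible slight loss of efficiency when costs are skewed.
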